### Study design

2.1

EvaClosure is a longitudinal cohort study of adults with AF and high risk of stroke and bleeding, based on two independent study populations: an SHI claims data population and the EvaClosure population—a subpopulation of patients recruited in the CLOSURE-AF trial. There is no patient-individual linkage of the CLOSURE-AF trial data with the SHI claims data; however, since information from both data sources converge in the health economic evaluation, statistical matching is used to establish maximum similarity between both study populations.

Pseudonymized CLOSURE-AF trial data are used for matching, including study participants' demographic information (e.g., gender, age), medical history and comorbidities, therapy (treatment arm, medications), the CHA_2_DS_2_VASc and HAS-BLED scores, as well as periprocedural events, complications, and adverse events. A matched sample is drawn from the eligible SHI population, for which the utilization of healthcare services and corresponding costs are determined. The basis of data for the health economic evaluation and Markov modeling is supplemented by primary data on quality of life collected using the EQ-5D-5L instrument (33, 34) aggregated to QALYs, as well as information on further health resource usage captured by the validated and standardized FIMA^4^ questionnaire (35, 36) [modified version, see the section “Outcome measures and analyses” (A2) for details on the modifications]. The survey-based data are collected within the CLOSURE-AF trial every six months up to two years after patient inclusion.

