#### Trial data collection

2.2.3

Data collection on health-related quality of life within CLOSURE-AF began in March 2018 and ended in November 2024. Data on the use of health resources based on a modified version of the FIMA questionnaire^5^ were collected by standardized interviews conducted by a trained study nurse. Data were collected every 6 months and intended to cover a two-year period starting from baseline. According to the CLOSURE-AF study visit plan, patients were asked to complete the FIMA interview at baseline as well as at visit number V5–V8 (see Supplementary Table S2 in Supplementary Appendix A). Up to five observation points were planned for each patient, including baseline. Because the EvaClosure substudy started later than the main clinical trial, informed consent for some patients was obtained retrospectively starting from January 2021. For the retrospectively enrolled EvaClosure participants, the FIMA was used at the first possible visit. As a result, for patients who consented to EvaClosure at V8, that is 24 months after inclusion in the clinical trial, there was only one measurement point. For consecutively enrolled patients, a two-year follow-up with five measurement points was scheduled. An overview of the visit schedule and the respective data collected is provided in Supplementary Table S2 in Supplementary Appendix A.

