In addition, patient-reported information on health service utilization collected in the EvaClosure study (captured by the FIMA questionnaire as described in the trial data collection section) will be used to validate and supplement the claims data–based cost estimates. Moreover, information on non-medical direct and further indirect costs will be used to calculate societal costs that cannot be determined from SHI claims data. The FIMA questionnaire captures the use of services from general practitioners and specialists, outpatient treatment in hospitals, allied health services, nursing care, partial inpatient care, short-term care, and non-medical services such as housekeeping, assistance from family/friends, and use of other nursing care benefits, over the past three months (35). Similar questions encompass the utilization of inpatient treatment and rehabilitation services, medical devices, and day clinic services in the past 12 months, as well as sociodemographic and socioeconomic data. A validation study based on routine health insurance data (36) showed that resource consumption can be determined validly and reliably by the FIMA questionnaire. Patient-reported health service utilization will then be valued using the valuation rates calculated per observation year in this study, as described by Bock et al. (42) and Muntendorf et al. (43). To cover all components relevant to the target group of EvaClosure patients and to ensure that FIMA data collection is organizationally consistent with the clinical trial visit plan, the questionnaire was slightly modified by the authors of this paper^7^. In particular, the following modifications were made:

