Because patients are surveyed with the FIMA every six months, questions on resource utilization covering a period of 12 months (see above) were modified to cover a period of six months.Information on sociodemographic and socioeconomic data as well as on drug utilization is collected in the CLOSURE-AF study. Therefore, questions covering these topics (e.g., on sex, age, marital status, and drug utilization within the last seven days) were waived.To estimate the indirect costs, two questions on unemployability (i.e., duration within the last six months and profession) were added.Using descriptive statistics, measures of location and dispersion will be compared for similarity. Difference-in-differences estimation will be applied to evaluate the incremental costs of the LAAC procedure by comparing the costs of services incurred by the intervention group and the control group. The time frame covers five years, comparing the average costs of both groups before and after the quarter of LAAC or first treatment with one of the pharmaceuticals defined as best medical treatment in the study design section.

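### Three-month FIMA recall at six-monthly interviews leaves nursing and informal care in months 0–3 after baseline unobserved, which matters for the societal ICER

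*Protocol article*

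**What the plan says.** All references are to the protocol article.

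- **Schedule (2.2.3, Trial data collection).** "Data were collected every 6 months and intended to cover a two-year period starting from baseline". Also, "patients were asked to complete the FIMA interview at baseline as well as at visit number V5–V8"; V8 is identified as 24 months after inclusion. Patients who consented late were first interviewed at the earliest visit still available, so some have a single interview.
- **Recall (2.4.2, A2).** One group of items covers physician contacts, hospital outpatient care, allied health services, several forms of nursing care, "housekeeping, assistance from family/friends, and use of other nursing care benefits, over the past three months". A second group (inpatient care, rehabilitation, devices, day clinic) had a 12-month recall in the published instrument.
- **Modifications (2.4.2).** Because the interview is six-monthly, "questions on resource utilization covering a period of 12 months (see above) were modified to cover a period of six months". In addition, "two questions on unemployability (i.e., duration within the last six months and profession) were added". No change to the three-month group is listed.
- **Use of the data (2.4.2).** FIMA reports "will be used to validate and supplement the claims data–based cost estimates". Information on non-medical direct and further indirect costs "will be used to calculate societal costs that cannot be determined from SHI claims data".
- **Linkage (2.1).** "There is no patient-individual linkage of the CLOSURE-AF trial data with the SHI claims data".

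**The concern.** The authors recognised that recall should match the interview interval. They shortened the items that would have overlapped, but list no step for the items that leave gaps. The three-month items therefore cannot cover the two years that the section on trial data collection sets out to cover.

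The position of the gaps matters more than their total length. A steady pattern of use can be estimated from one quarter in each half-year. The first quarter after baseline is different: one arm undergoes a one-time procedure and the other does not, so use in that quarter is least likely to resemble use in months 3–6. The month-6 interview looks back only to month 3, so no scaling of its answers can recover what happened before.

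At stake are the nursing-care, housekeeping and family-help components of societal cost. The SHI data listed in 2.3.2 do not include them, and without patient-level linkage claims could not fill the gap for trial patients in any case. These components feed the societal ICER, one of the two perspectives in the objectives.

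**Working it through.** The article gives no coverage figure, so there is none to reproduce. The sample size calculation does not bear on this point.

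**Inputs**
- Interviews at months 0, 6, 12, 18 and 24 (2.2.3: baseline and V5–V8, six-monthly, V8 = month 24).
- Recall R = 3 months for the nursing, informal-care, outpatient and allied-health items; R = 6 months for the adapted items and the work-incapacity item (2.4.2).

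**Coverage.** An interview at month v covers the window from v − R to v. The baseline interview covers only time before inclusion.

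| First FIMA interview in follow-up | 3-month items | 6-month items |
|---|---|---|
| Month 6 (four interviews) | 4 × 3 = 12 of 24 (50%) | 4 × 6 = 24 of 24 (100%) |
| Month 12 (three) | 3 × 3 = 9 of 24 (37.5%) | 3 × 6 = 18 of 24 (75%) |
| Month 18 (two) | 2 × 3 = 6 of 24 (25%) | 2 × 6 = 12 of 24 (50%) |
| Month 24 only (one) | 1 × 3 = 3 of 24 (12.5%) | 1 × 6 = 6 of 24 (25%) |

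For the fully followed patient, the three-month windows are months 3–6, 9–12, 15–18 and 21–24. Months 0–3, 6–9, 12–15 and 18–21 are uncovered.

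**What scaling can repair.** Doubling the reports at months 12, 18 and 24 represents 3 × 6 = 18 months. The month-6 report, used as it stands, represents 3 more. That leaves 24 − 21 = 3 months, namely months 0–3.

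**What doubling the month-6 report would do.** Let u(0–3) and u(3–6) be mean use in an arm in the two quarters.
- Error in an arm = 2·u(3–6) − [u(0–3) + u(3–6)] = u(3–6) − u(0–3).
- Error in the difference between arms = [u(3–6) − u(0–3)] for LAAC − [u(3–6) − u(0–3)] for control.

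This is zero only if use changes equally between the two quarters in both arms. Extra early care after LAAC pushes the difference in LAAC's favour; extra early care in controls pushes it the other way. The article gives neither quantity.

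**Time from baseline to procedure.** It is not stated. If LAAC takes place L months after baseline (0 ≤ L ≤ 3), the first three post-procedure months run from L to L + 3, and L of them fall in the observed 3–6 window. Assumed lags of 0, 0.5 and 1 month leave 3, 2.5 and 2 of the 3 months unobserved.

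**The case against.** Much of the case on the other side stands.

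- **Claims carry the main cost estimate.** Outpatient and allied-health costs are in the SHI data (2.3.2), and the comparison is made before and after the quarter of LAAC or first medical treatment (2.4.2). A reader might infer that half of follow-up is lost for all outpatient costs. The document does not support that: for these items the FIMA only validates and supplements.
- **Rescaling is analysis-plan detail.** Nothing says that reports will be summed unscaled or compared with claims over unequal periods, so neither can be treated as planned. But an analysis plan can only rescale what was asked, and months 0–3 were not.
- **Early complications are partly covered.** Inpatient, rehabilitation, device, day-clinic and work-incapacity items have six-month recall and are unaffected.
- **Direction is not established.** A reader might infer that all post-LAAC care is missed, in one arm only, in LAAC's favour. The lag to the procedure is not given, and the same windows are unobserved in controls, including care after early events. Nor can a euro amount be derived, since the article gives no hours or unit prices.
- **Three months is the published instrument's own window**, and the article cites a validation study. Keeping it to limit recall error is defensible, but the article does not give that reason, and the gap would still need handling.

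The list of modifications is introduced as a selection of particulars, so an unlisted change is possible. Nothing in the text points to one.

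**Conclusion.** The mismatch is real and follows from the article's own statements. At best, the three-month items observe 12 of 24 months. Of the uncovered time, 9 months can reasonably be represented by scaling and 3 months (0–3 after baseline) cannot. The consequence is confined mainly to nursing care, housekeeping and family help in the societal ICER; physician and allied-health contacts are affected only in the FIMA's supplementary role.

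Extra early care of these kinds after LAAC would be missed, but the net direction and size of any bias are not known from the document. The conclusion assumes that the listed modifications are complete, that V5–V7 fall at months 6, 12 and 18 as the six-monthly schedule implies, and that the procedure usually takes place soon enough after baseline for most of the early post-procedure period to fall in months 0–3.

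**What to change.** Data collection has ended, so the change lies in the analysis and reporting:

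1. State that the three-month items cover months 3–6, 9–12, 15–18 and 21–24 in a fully followed patient, and less in those enrolled retrospectively.
2. Scale these items separately from the six-month items, using a factor of 2 for months 6–24.
3. Do not fill months 0–3 from the month-6 interview.
4. For claims-recorded items (physician and allied-health care), rely on the matched SHI groups for the first post-index quarter.
5. For nursing and informal care in months 0–3, run a sensitivity scenario that varies the quantity in both arms, and report the societal ICER with the resulting range.
6. When FIMA reports of these items are used to validate claims, compare them only over identical three-month windows.

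Cost: some wording and one extra scenario, with no new data. The societal result will rest on one more stated assumption and have a wider range around it.

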The CLOSURE-AF-DZHK16 study addresses this research gap. CLOSURE-AF is a prospective, randomized clinical trial involving 42 study centers in Germany^1^ that analyzes the clinical benefit of LAAC in patients with non-valvular AF (NVAF) at high risk of stroke and bleeding (high-risk group)^2^ compared with best physician–directed medical care (including anticoagulation, when tolerated). Patient enrollment began in February 2018, with a study completion date in November 2024. Subjects were randomized 1:1 in the intervention and control group, receiving either catheter-interventional LAAC with a CE-certified LAA occluder (e.g., Watchman™, Amplatzer Amulet) or physician-directed best medical care [NOACs or vitamin K antagonists (VKA), antiplatelet therapy, no antithrombotic/antiplatelet therapy in case of contraindications] chosen at the discretion of the treating physician (23).

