### Outcome measures and analyses

2.4

The EvaClosure study design consists of four modules that build on one another (see Table 2). For module A1, a cost-of-illness study assesses direct and indirect costs associated with a high risk of stroke and bleeding in patients with AF. Focusing on the high-risk group only, module A2 compares direct and indirect costs associated with LAAC treatment to best medical care. Module B1 quantifies the utility effect of LAAC in terms of QALYs gained compared with standard of care via data of the EvaClosure study population. The subsequent module B2, on the other hand, combines SHI claims data and data from the EvaClosure study population as well as CLOSURE-AF trial results to conduct a cost–utility analysis.

**Table 2 T2:** Overview study modules, design, and outcome measures.

Module	Main Objectives	Study population	Design	Time frame	Costs/Outcomes
A1	To assess cost of illness to high-risk of stroke and bleeding in patients with AF	SHI study population, divided into the high-risk AF group and the AF group without high risk	Longitudinal cohort study, retrospective (difference-in-differences)	2015–2021; 1 year before and 4 years after inclusion per individual	direct and indirect costs
A2	To assess direct and indirect costs of LAAC intervention vs. best available medical care in high-risk patients with AF	EvaClosure study population: high-risk AF patients divided into intervention and control groups as per the CLOSURE-AF protocol.	Longitudinal cohort study, prospective (difference-in-differences)	2018–2025; enrollment starting in 01/2021 with a follow-up of up to 24 months	Direct and indirect costs
		SHI study population: the high-risk AF group divided into intervention and control groups as close as possible to the CLOSURE-AF protocol	Longitudinal cohort study, retrospective (difference-in-differences)	2015–2021; 1 year before and 4 years after inclusion per individual	
B1	To assess the utility effect of LAAC compared with best medical care	EvaClosure study population: high-risk AF patients divided into intervention and control groups as per the CLOSURE-AF protocol	Longitudinal cohort study, prospective	2018–2025; CLOSURE-AF enrollment starting in 03/2018; obtaining informed consent for prospective and retrospective participation in EvaClosure started in 01/2021, patient individual follow-up of up to 24 months	Health-related quality of life, QALYs

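### Module A2 uses difference-in-differences for FIMA costs in arms randomised 1:1; this is unbiased but in general less precise than adjusting for the baseline cost already collected

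*Protocol article*

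**What the plan says.** Table 2 (section 2.4) gives module A2 two data sources. For the EvaClosure population the groups are "high-risk AF patients divided into intervention and control groups as per the CLOSURE-AF protocol", and the design entry begins "Longitudinal cohort study, prospective (difference-in-differences". The retrospective claims cohort gets the same method. Section 1.1 says of the trial: "Subjects were randomized 1:1 in the intervention and control group".

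Section 2.4.2 repeats the method without separating the two sources: "Difference-in-differences estimation will be applied to evaluate the incremental costs of the LAAC procedure by comparing the costs of services incurred". The contrast is described as "comparing the average costs of both groups before and after the quarter of LAAC or first treatment" over a five-year frame. No baseline-adjusted model is named for A2.

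On the FIMA schedule, section 2.2.3 says that "patients were asked to complete the FIMA interview at baseline as well as at visit number V5–V8" and "Up to five observation points were planned for each patient, including baseline". It adds: "For consecutively enrolled patients, a two-year follow-up with five measurement points was scheduled". Participants who consented retrospectively first completed FIMA at the next visit possible, and those who consented at 24 months have a single record.

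Section 2.4.2 uses FIMA to check and complement the claims-based costs and to supply societal cost items that claims do not contain. Section 2.4.4 carries these into the societal-perspective ICER.

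**The concern.** The only reason the article gives for difference-in-differences is in section 2.4.1: it should reduce unobserved structural differences that survive balancing. That reason belongs to non-randomised claims cohorts. In the EvaClosure population the arms come from 1:1 randomisation, and section 2.4.3 relies on that when it assumes equal baseline utilities and compares QALYs with a t-test. No reason is given for treating FIMA costs from the same patients differently.

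With one baseline, standard difference-in-differences is a change-score comparison: mean follow-up cost minus baseline cost, by arm. The baseline is one short-recall cost (three or six months, depending on the item) and is likely to be noisy. Subtracting it in full, rather than with a coefficient estimated from the data, adds variance that could be avoided. At stake is the width of the interval around the FIMA-based incremental cost, and through it the uncertainty shown for the societal ICER.

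**Working it through.** **The plan's own figure.** The article states no precision or power for the cost comparison. Its only sample-size calculation (section 2.2.2) is for the QALY test, and it reproduces: 0.004 / sqrt((0.015² + 0.003²)/2) = 0.370; n = 2(1.960 + 1.036)² / 0.37² = 131.1, so 132 per group and 264 in total; 264/0.90 = 293.3, so 294. It is used below only as a convenient size for simulation.

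**Inputs.** From the article: 1:1 randomisation (section 1.1); one baseline and four follow-ups, V5–V8 (section 2.2.3). Assumed, because the article does not give them: the correlation rho, taken as common to all pairs of visits, and equal variances at all visits (relaxed below).

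**Formulas.** Per-patient variance in units of the single-visit variance, with four follow-ups:

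- follow-up mean only: m = (1 + 3·rho)/4
- difference-in-differences: m + 1 − 2·rho
- baseline-adjusted (ANCOVA, large sample): m − rho²
- excess of difference-in-differences over ANCOVA: 1 − 2·rho + rho² = (1 − rho)²

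| rho | follow-up only | difference-in-differences | ANCOVA | variance ratio | SE ratio |
|---|---|---|---|---|---|
| 0.3 | 0.475 | 0.875 | 0.385 | 2.27 | 1.51 |
| 0.5 | 0.625 | 0.625 | 0.375 | 1.67 | 1.29 |
| 0.7 | 0.775 | 0.375 | 0.285 | 1.32 | 1.15 |
| 0.8 | 0.850 | 0.250 | 0.210 | 1.19 | 1.09 |

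Below rho 0.5, difference-in-differences is also less precise than ignoring the baseline: 0.875/0.475 = 1.84 at rho 0.3. With a single follow-up the ratios to ANCOVA are 1.54, 1.33 and 1.18 at rho 0.3, 0.5 and 0.7.

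**Skewed costs.** A simulation with lognormal costs, no treatment effect, 132 per arm and 4,000 replicates gave variance ratios of 2.38, 1.74 and 1.46 at rho 0.3, 0.5 and 0.7. All three estimators averaged close to zero, so none was biased.

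**Unequal variances.** With baseline SD 1 and follow-up SD s, the excess becomes (1 − rho·s)² and the ANCOVA variance s²(m − rho²).

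- s = 1.3, rho = 0.7: excess (1 − 0.91)² = 0.0081; ANCOVA 1.69 × 0.285 = 0.482; ratio 1.02.
- s = 1.5, rho = 0.5: excess (1 − 0.75)² = 0.0625; ANCOVA 2.25 × 0.375 = 0.844; ratio 1.07.
- s = 0.8, rho = 0.5: excess (1 − 0.40)² = 0.36; ANCOVA 0.64 × 0.375 = 0.24; ratio 2.50.

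The direction is fixed, because the excess is a square and cannot be negative. The size is not.

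**The case against.** **The wording in section 2.4.2 fits the claims data better.** Its five-year, quarter-based frame cannot describe FIMA, which runs for at most 24 months. This stands. The link to the randomised sample rests on the EvaClosure row of Table 2, which is explicit.

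**The coefficient of 1 is inferred.** A2 gives no model equation, and two-way fixed effects is spelled out only for A1. True, but that coefficient is what standard difference-in-differences means.

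**Late consenters.** A reader might infer that only patients with a baseline FIMA can enter the analysis. That holds for an individual change score. The article speaks of group averages, and a group-level version could use late consenters' follow-up records. It would not regain the precision. If 70% had a baseline (an assumption), the variance would be m + 1/0.7 − 2·rho = 1.30, 1.05 and 0.80 at rho 0.3, 0.5 and 0.7, against 0.475, 0.625 and 0.775 for follow-up only. Plain ANCOVA has its own gap here: it drops patients without a baseline, so the fix must deal with them.

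**Validity.** A reader might infer that the cost estimate is biased. The documents do not support that: under randomisation the method is unbiased. It over-corrects only conditionally, in a sample where the arms happen to differ at baseline.

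**Power.** It is tempting to turn the ratios into a loss from 85% power. That target belongs to the QALY test, and the article makes no power claim for costs.

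**Comparability.** Using one estimator in both sources makes it easier to set FIMA against claims. The article does not give this as its reason, but a sensitivity analysis would keep the benefit.

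**Conclusion.** The point holds as one of efficiency, not validity. For FIMA costs in the randomised EvaClosure sample, difference-in-differences is unbiased and, in large samples, never more precise than adjusting for baseline. Under equal variances and a common correlation its variance is about 2.3, 1.7 and 1.3 times as large at rho 0.3, 0.5 and 0.7. The true size is unknown, because the article gives neither rho nor cost SDs: it can be near nil if follow-up costs are more variable than baseline costs, and larger if they are less variable.

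The reach is limited. Only the FIMA-based part of the societal cost is affected; the rest comes from claims. A reader might infer that the whole societal ICER, or all of module A2, is undermined. The documents do not support that, and the effect on the ICER interval cannot be computed from them. The use of difference-in-differences in the non-randomised claims cohorts is not in question.

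**What to change.** Keep difference-in-differences for the SHI claims cohorts. In Table 2 (EvaClosure row of A2) and section 2.4.2, make the main analysis of FIMA costs one of the following:

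- a regression of follow-up cost on randomised arm and baseline FIMA cost, with missing baselines imputed; or
- a constrained longitudinal model with a common baseline mean for both arms, so that late consenters without a baseline FIMA are retained.

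Use robust or bootstrap standard errors because costs are skewed, and carry this estimate and its uncertainty into the societal-perspective ICER. Report difference-in-differences as a sensitivity analysis for comparison with the claims estimates.

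The change needs a few sentences of wording, no new data and no further patients. The downsides are small: claims and trial contrasts will come from different models, and the handling of missing baselines must be stated.
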